Inclusion Criteria for all study participants: (1) Adult women (≥18 years of age) with a histologically confirmed gynecological malignancy (cervical, endometrial, vulvar, or vaginal), of any stage, who have completed a course of pelvic RT and/or CT. (2) Ability to understand and willingness to sign the study-specific Informed Consent Form. Additional criteria for inclusion in the OT Group: Presence of chronic R/CIPT, with a duration of ≥3 months following conventional symptomatic management. A toxicity grade of 2 (moderate symptoms; limiting instrumental activities of daily living) or higher, as per the CTCAE v5.0.

Exclusion Criteria for all study participants: any of the following will preclude inclusion: (1) Failure to meet all the inclusion criteria specified above. (2) Unwillingness or inability to provide written informed consent for study participation. (3) Presence of active inflammatory bowel disease (e.g., Crohn’s Disease, Ulcerative Colitis) or a history of major gastrointestinal resection (excluding appendectomy) that could significantly alter gut anatomy and microbiota. (4) Any uncontrolled intercurrent illness or psychiatric condition that, in the investigator’s opinion, would limit compliance with study requirements or interfere with the interpretation of results.

Withdrawal Criteria. Participants will be withdrawn from the study under the following circumstances: (1) Voluntary Withdrawal: At the patient’s own request, at any time and for any reason, without any penalty or impact on their future clinical care. (2) Loss to Follow-up: Inability to contact the patient or their failure to attend scheduled study visits. (3) Clinical Decision: Withdrawal by the principal investigator due to the occurrence of an adverse event, intercurrent illness, or any other clinical reason that justifies discontinuation for the patient’s well-being or the integrity of the study. (4) Protocol Violation: Significant deviation from the study protocol.

All patients, regardless of their decision to participate, decline, or withdraw from the study, will continue to receive standard oncological care and follow-up from their treating physicians. Withdrawal from the study will not affect their access to routine or compassionate medical treatments, including ozone therapy if clinically indicated.

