Microbiological & Biomarker Endpoints: Primary Microbiological Endpoint: Changes in gut microbiota composition and diversity. Method: 16S rRNA gene sequencing (Illumina MiSeq platform) of stool samples. Analysis: Differential abundance of key taxa (e.g., Faecalibacterium, Roseburia, Akkermansia vs. Proteobacteria), and alpha/beta-diversity indices. Biomarker Endpoints: Serum samples will be cryopreserved at −80 °C in a registered biobank for subsequent batch analysis of inflammatory cytokines and oxidative stress markers.

Clinical Endpoints: Primary Clinical Endpoint: Pelvic and gynecological toxicity grade measured by: (1) CTCAE v5.0 scale, and (2) EORTC QLQ-CX24 module (cervical cancer-specific). Secondary Clinical Endpoints: (1) Quality of Life (QoL) measured by: EORTC QLQ-C30 (for cancer patients) and EQ-5D-5L™ (for the general population), (2) Psychological Status: Hospital Anxiety and Depression Scale (HADS), and (3) serum inflammatory/oxidative stress biomarker analysis.

Methodology: Sampling Schedule, Assays, and Statistical Approaches. Study Design: Prospective, observational study. Sample Size: 38 patients (19 with toxicity and OT, 19 matched controls without toxicity). Sampling Schedule: (1) R/CIPT Group: Baseline (pre-ozone) and post-treatment (after the final ozone session). (2) Control Group: A single time point during a routine follow-up visit.

Assays: Microbiota: Stool samples for DNA extraction and 16S rRNA sequencing. Inflammatory cytokines and oxidative stress markers: serum samples. The researchers analyzing the stool and serum samples will be blinded regarding the sample’s group assignment (non-toxicity control, pre-ozone, post-ozone).

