The analysis of serum biomarkers will encompass a comprehensive panel to evaluate both oxidative stress and inflammatory status. 1. Oxidative Stress Biomarkers: The assessment will include global oxidative stress markers such as FRAP (Ferric Reducing Ability of Plasma), which measures antioxidant capacity; dROMs (Reactive Oxygen Metabolites), which determines the peroxidation potential; and BAP (Biological Antioxidant Potential). Specific molecular biomarkers will also be quantified, including the activity of the key antioxidant enzymes Superoxide Dismutase (SOD) and Catalase (CAT), the levels of reduced glutathione (GSH) as a critical cellular antioxidant, Advanced Oxidation Protein Products (AOPP) as a marker of protein damage, and ROOH (Total Hydroperoxides) to assess the primary oxidation products of lipids and other molecules. 2. Inflammatory Biomarkers: The inflammatory profile will be characterized by measuring a panel of Pro-inflammatory Cytokines: Tumor Necrosis Factor-alpha (TNF-α), Interleukin-6 (IL-6)**,** Interleukin-1 beta (IL-1β), and Interleukin-8 (IL-8/CXCL8)**.** Furthermore, systemic inflammation will be evaluated through established clinical markers: C-Reactive Protein (CRP) and VES (Erythrocyte Sedimentation Rate)**.**

Statistical Approaches: Primary Analysis: Non-parametric tests will be used due to the small sample size (Wilcoxon signed-rank for pre/post ozone, Mann–Whitney U for inter-group comparisons). Spearman correlations for microbiota-clinical parameter associations. All variables will be described as medians and quartiles 1–3 (percentiles 25–75%). *p*-values less than 0.05 will be considered significant, and all hypothesis tests will be conducted two-sided. Software: R (v4.5.0 or higher).

This study is the first to prospectively explore the novel hypothesis that the clinical benefits of rectal OT for chronic R/CIPT could be mediated, in part, through gut microbiota modulation. The proposed mechanistic pathway is: Ozone → Attenuation of local oxidative stress and inflammation (via Nrf2 activation and NF-κB inhibition) → Restoration of a healthy mucosal microenvironment → Promotion of commensal bacteria (e.g., SCFA producers) and suppression of pathobionts → Improved barrier function and reduced systemic inflammation → Clinical improvement in toxicity and Quality of Life.

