Sampling & Follow-Up	Design: Prospective, observational study. Blinding: Sample analysis will be blinded to group assignment.	OT Group: Stool/serum samples at Baseline (pre-ozone) and post-treatment (week 16). Control Group: A single sample taken at routine follow-up.	Confounders: Strict recording of recent use of antibiotics and probiotics.
Clinical & Biomarker Endpoints	Objective: Evaluate the effect of Ozone on toxicity and systemic status.	Clinical Assessments: Toxicity: CTCAE v5.0 and EORTC QLQ-CX24. Quality of Life (QoL): EORTC QLQ-C30 and EQ-5D-5L™. Psychological Status: HADS.	Biological Samples: Microbiota analysis (16S rRNA gene sequencing), Inflammatory Cytokines and Oxidative Stress Markers (serum).
Analysis & Conclusion	Core Hypothesis: Ozone modulates gut microbiota (weeding and seeding) → reduces inflammation → clinical improvement.	Analysis: Non-parametric tests (Wilcoxon, Mann–Whitney U) due to small sample size (*n* = 38). Significance: *p* < 0.05.	Limitation: Observational design and sample size prevent definitive causal conclusions.

Legend: R/CIPT: Radiotherapy/Chemotherapy-Induced Pelvic Toxicity; OT: Ozone Therapy. CTCAE: Common Terminology Criteria for Adverse Events (v5.0), a standardized scale for toxicity grading; EORTC QLQ-CX24: European Organization for Research and Treatment of Cancer Quality of Life Questionnaire—Cervical Cancer Module; EORTC QLQ-C30: European Organization for Research and Treatment of Cancer Quality of Life Questionnaire—Core Module (for cancer patients); EQ-5D-5L™: EuroQol-5 Dimensions-5 Levels, a standardized instrument for measuring general health-related Quality of Life; HADS: Hospital Anxiety and Depression Scale; 16S rRNA: 16S ribosomal Ribonucleic Acid gene sequencing, used to identify and quantify microbial populations; QoL: Quality of Life.

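### The protocol provides only for withdrawal from the study, not for stopping ozone while staying under observation, so selective losses can tilt the pre/post comparison towards ozone

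*Protocol article*

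**What the plan says.** All of this is in the protocol article, section 5 (Proposed Clinical Study/Protocol) and Table 1.

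- **Level of withdrawal.** The Withdrawal Criteria open with "Participants will be withdrawn from the study under the following circumstances". Four circumstances follow, and all of them end study participation.
- **Clinical grounds.** The third is "Withdrawal by the principal investigator due to the occurrence of an adverse event, intercurrent illness, or any other clinical reason that justifies discontinuation". The sentence then gives the patient's well-being or the integrity of the study as the justification, so this is an investigator's judgement.
- **Deviation.** The fourth is "Protocol Violation: Significant deviation from the study protocol". What counts as significant is not defined.
- **Missed visits.** Loss to follow-up covers "Inability to contact the patient or their failure to attend scheduled study visits".
- **Treatment and participation are separable.** The closing paragraph states: "Withdrawal from the study will not affect their access to routine or compassionate medical treatments, including ozone therapy if clinically indicated".
- **One post-baseline assessment.** The Sampling Schedule for the toxicity group reads "Baseline (pre-ozone) and post-treatment (after the final ozone session"; Table 1 has "Stool/serum samples at Baseline (pre-ozone) and post-treatment (week 16".
- **Analysis.** The Statistical Approaches name "Wilcoxon signed-rank for pre/post ozone" for change within the ozone group, and the Mann–Whitney U test for comparisons between groups, two-sided at 0.05.

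**The concern.** Two decisions are merged into one. Stopping ozone is a treatment event. Leaving the study ends data collection. The criteria define only the second, although some of the listed reasons bear mainly on the first.

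With one follow-up assessment and a paired test, a patient withdrawn before that assessment contributes nothing to the pre/post contrast. Adverse events, intercurrent illness and clinical deterioration are plausibly related to the toxicity grade and quality-of-life scores being measured. The pairs that remain may then over-represent patients who did well, and the median change would look better than it was among all who started. The limitations listed at the end of section 5 cover design, sample size, the single control time point, the sequencing method and recorded confounders, but not selective loss.

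This is a rule the article states, not a detail it leaves to an analysis plan. No later plan can recover a stool or serum sample that was never taken. Nor does the design require observation to stop: the study is observational, and study participation is already kept apart from access to ozone.

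**Working it through.** **The plan's own figure.** The sample size is 19 + 19 = 38. No effect size, SD, power or dropout rate is given, so 38 cannot be derived further and the number withdrawn has to be assumed. There are at most 19 pre/post pairs.

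**Step 1: who leaves which comparison.**

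| Comparison | Test | Needs | Effect of withdrawal after baseline |
|---|---|---|---|
| Ozone group, pre vs post | Wilcoxon signed-rank | both values per patient | patient drops out |
| Ozone group at baseline vs controls | Mann–Whitney U (unpaired) | one value per patient | none; the sample is already taken |

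**Step 2: expected shift.** Assumptions: the true change is zero in all 19, changes follow N(0,1) with positive values favourable, and k patients are withdrawn at random from the 10 worst changes. The expected mean of the 10 worst of 19 standard normal values is about −0.726. All 19 average zero, so the remaining patients average

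shift = k × 0.726 / (19 − k).

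- k = 1: 0.726 / 18 = 0.04 SD
- k = 2: 1.452 / 17 = 0.085 SD
- k = 3: 2.178 / 16 = 0.14 SD
- k = 4: 2.904 / 15 = 0.19 SD
- k = 5: 3.630 / 14 = 0.26 SD

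**Step 3: error of the signed-rank test.** Same model, 20,000 simulated studies per setting, two-sided 0.05.

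| Withdrawn | Pairs left | Mean shift (SD) | Rejection | Rejection in favour of ozone |
|---|---|---|---|---|
| 0 | 19 | 0.00 | 5.0% | 2.4% |
| 1 | 18 | 0.04 | 4.8% | 3.3% |
| 2 | 17 | 0.09 | 5.1% | 4.4% |
| 3 | 16 | 0.14 | 6.3% | 5.8% |
| 4 | 15 | 0.19 | 9.7% | 9.4% |
| 5 | 14 | 0.26 | 14.0% | 13.8% |

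Shorter runs of the same model gave 5.9–6.6%, 8.6–10.0% and 12.8–14.0% for three, four and five withdrawals.

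**Step 4: a second model.** Here withdrawal depends on a score with correlation rho to a poor change (5,000 runs per setting).

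| Withdrawal rate | Pairs left | rho 0: rejection | rho 0.5: shift, rejection | rho 1: shift, rejection |
|---|---|---|---|---|
| 5% | 18 | 4.8% | 0.05 SD, 5.5% | 0.10 SD, 7.6% |
| 10% | 17 | 4.1% | 0.10 SD, 6.4% | 0.19 SD, 13.7% |
| 20% | 15 | 4.5% | 0.18 SD, 10.3% | 0.35 SD, 34.5% |
| 30% | 13 | 4.1% | 0.25 SD, 13.3% | 0.50 SD, 58.3% |

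The column rho = 1 removes exactly the worst changes and is an extreme, not an expectation. At rho = 0 there is no bias, only lost precision.

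**Step 5: precision.** Using the noncentral t distribution with effective size 0.955 × n (the efficiency of the signed-rank test under normality), the change detectable with 80% power is about 0.70 SD with 19 pairs, 0.74 with 17, 0.80 with 15 and 0.87 with 13.

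**The case against.** Much of the case on the other side stands, and it limits the point.

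- **A reader might infer that every adverse event removes the patient.** The text makes it the investigator's decision, on grounds of well-being or study integrity. It is not automatic.
- **A reader might infer that patients who stop because ozone does not help are withdrawn.** Lack of benefit is not a listed reason. The regimen is described as usually 40 sessions, so a short course is not clearly a significant deviation. An early stopper also has a final session after which a sample could be taken, provided the patient has not been withdrawn.
- **A reader might infer that each lost patient's matched control is lost too.** The planned comparison between groups is unpaired, so no control drops out. The baseline sample of a withdrawn patient is already in hand, and nothing says that it is discarded.
- **A reader might infer that the microbiota result is biased.** That needs poor tolerance to go with unfavourable microbial change. The article gives no such link, and without one the error stays at 4–5%.
- **The losses may be few.** Section 3 reports, from cited experience, no serious adverse events and only transient meteorism. That points to few adverse-event withdrawals, and with one or two losses the error is not inflated.
- **The article is condensed, and the study is a pilot that disclaims definitive causal conclusions.** Analysis sets and missing-data handling may well be in documents not shown.

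What remains is that the stated rule ends participation, the only follow-up measurement comes at the end, and an uncollected sample cannot be restored by analysis.

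**Conclusion.** The point holds as a weakness in a stated rule, worth correcting before enrolment. Patients withdrawn before the post-treatment assessment leave the pre/post comparison of the primary endpoints for reasons that may be related to outcome. The direction would favour ozone if withdrawal goes with a poor course; this is plausible for toxicity and quality of life and only possible for microbiota.

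The size cannot be stated from the documents. Under the worse-half assumption it is negligible for the error rate at one or two withdrawals. At three to five it rises to about 6–7%, 10% and 14%, with shifts of about 0.14, 0.19 and 0.26 SD. These figures rest on an assumed number withdrawn, an assumed link with outcome, and normally distributed changes. They show that a handful of selective losses among 19 matters, not that such losses will occur. The documents do not support calling the pre/post result biased as planned, and the baseline comparison with controls is not touched.

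**What to change.** 1. In the Withdrawal Criteria, distinguish *ozone stopped* from *withdrawn from the study*.
2. Let data collection end only when consent is withdrawn or loss to follow-up is unavoidable. Adverse events, intercurrent illness, other clinical reasons and protocol deviations are recorded, but do not by themselves end observation of a consenting patient.
3. Ask consenting patients who stop early or deviate for the same week-16 stool and serum samples, CTCAE grading and questionnaires. State the time point once, because the Sampling Schedule ties it to the last session and Table 1 to week 16; these differ for an early stopper.
4. Take all patients who started ozone and have the post assessment as the primary pre/post set, with completers of the course as a sensitivity analysis. Report the number and reasons for those without a post assessment.

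The cost is a wording change plus the effort of obtaining a few follow-up assessments from early stoppers. When or how ozone is stopped remains a clinical decision and is not addressed here.

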## 3. Biological Mechanisms of Ozone Therapy

OT exerts its biological effects primarily through the controlled generation of reactive oxygen species (ROS) and lipid peroxides (LOPs) upon contact with biological fluids. These molecules act as secondary messengers, triggering redox-sensitive signaling pathways such as Nrf2/Keap1/ARE, which upregulate antioxidant defenses and restore redox homeostasis. The hormetic response to low-dose ozone is characterized by a transient, moderate oxidative stress that stimulates cellular adaptation without causing cytotoxicity [29,30,31,32,33].

OT enhances microcirculation and tissue oxygenation by improving rheological properties of blood, increasing erythrocyte flexibility, and promoting oxygen release to hypoxic tissues. Clinical studies have demonstrated increased tissue oxygenation following systemic ozone administration, particularly in ischemic conditions [34,35].

The anti-inflammatory and immunomodulatory properties of ozone are mediated by downregulation of pro-inflammatory cytokines (e.g., TNF-α, IL-1β) and upregulation of anti-inflammatory mediators. Ozone modulates immune cell function, including regulatory T lymphocytes, and shifts cytokine profiles toward an anti-inflammatory state. This is achieved through redox signaling and direct effects on immune cell populations [10,36,37].

Emerging preclinical evidence suggests that ozone therapy, especially via rectal insufflation or ozonated water, can directly and indirectly impact the gut microbiota. Ozone administration has been shown to increase the abundance of beneficial bacteria (e.g., Lactobacillus, Bifidobacterium), restore microbial diversity, and modulate microbial metabolites such as SCFAs and tryptophan derivatives. These changes contribute to improved intestinal barrier function and reduced inflammation in models of atherosclerosis and sepsis [12,13,38].

Overall, OT acts as a redox bioregulator, with pleiotropic effects on cellular signaling, tissue oxygenation, inflammation, immune modulation, and the gut microbial ecosystem [39].

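### Reduced glutathione, SOD and catalase are assigned to stored serum, so a difference in them cannot be read as a cellular antioxidant response

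*Protocol article*

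**What the plan says.** All references are to the protocol article.

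- **Specimen.** In section 5, the biomarker endpoint text reads "Serum samples will be cryopreserved at −80 °C in a registered biobank for subsequent batch analysis of inflammatory cytokines and oxidative stress markers". The assay list repeats it: "Inflammatory cytokines and oxidative stress markers: serum samples". The panel description opens with "The analysis of serum biomarkers will encompass a comprehensive panel to evaluate both oxidative stress and inflammatory status". Table 1 also gives serum for the inflammatory and oxidative markers. No whole blood, red-cell lysate or other cell fraction is named.
- **Markers.** Eight oxidative stress markers are listed: FRAP, dROMs, BAP, SOD, catalase, reduced glutathione (GSH), AOPP and ROOH. GSH is introduced as "the levels of reduced glutathione (GSH) as a critical cellular antioxidant". SOD and catalase are to be measured as enzyme activity.
- **Rank and timing.** "serum inflammatory/oxidative stress biomarker analysis" is a secondary endpoint. Table 1 places the ozone group's samples at baseline and week 16, and the controls' single sample at a routine follow-up visit.
- **Testing.** Wilcoxon signed-rank within the ozone group (n = 19) and Mann–Whitney between groups, two-sided at 0.05.
- **Rationale.** Section 3 describes ozone as "triggering redox-sensitive signaling pathways such as Nrf2/Keap1/ARE, which upregulate antioxidant defenses and restore redox homeostasis". The pathway in section 5 places the Nrf2 step at the tissue: "Attenuation of local oxidative stress and inflammation (via Nrf2 activation and NF-κB inhibition".

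**The concern.** The article calls GSH cellular and then assigns it to a fluid from which the cells have been removed. Catalase and SOD in blood also sit largely inside cells. What remains in serum is a small extracellular amount. For GSH, that amount is in the reduced form, which can oxidise in the tube. All three can be raised by red cells that break at the draw.

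Unlike a test that cannot be run on the specimen, these assays will return plausible numbers, and those numbers will be tested at 0.05. In a paper whose rationale is an upregulated antioxidant defence, readers will tend to take a rise in GSH, SOD or catalase as support for it and a flat result as evidence against it. Serum supports neither reading. Section 5 also looks ahead to oxidative stress biomarkers of treatment response, so a misread result could be carried into the next trial.

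**Working it through.** The article gives no concentration, SD, effect size or power for these markers, so there is no figure of its own to reproduce. Everything numerical below rests on assumed inputs and shows ranges only.

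**1. Text comparison.** Stated quantity: GSH as a cellular antioxidant, plus activity of two largely intracellular enzymes. Stated specimen: serum, in four places. Serum is by definition cell-free, so the specimen does not contain the cellular pool. This step needs no assumption about handling.

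**2. Red-cell leakage.** Amount added to serum, as a share of the true serum level = R × h × Hct / (1 − Hct), where R is the red-cell to serum concentration ratio, h the fraction of red cells lysed, and Hct the haematocrit (assumed 0.40, so the last factor is 0.40/0.60 = 0.667).

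| R (assumed) | h = 0.05% | h = 0.1% | h = 0.5% |
|---|---|---|---|
| 10 | 0.33% | 0.67% | 3.3% |
| 100 | 3.3% | 6.7% | 33% |
| 1000 | 33% | 67% | 333% |

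For GSH alone, assume 1–3 mmol/L in red cells and 1–5 µmol/L in serum. At h = 0.1% the addition is 1000 × 0.001 × 0.667 = 0.67 µmol/L up to 3000 × 0.001 × 0.667 = 2.0 µmol/L. Relative to serum that is 0.67/5 = 13% up to 2.0/1 = 200%. Leakage can be trivial or dominant.

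**3. Loss of reduced GSH before freezing, if nothing stabilises it.** Fraction left = 0.5^(time / half-life). With an assumed half-life of 10–60 minutes, 30 minutes of clotting leaves 0.5^3 = 12.5% to 0.5^0.5 = 71%.

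**4. Effect on the pre/post test.** Simulated Wilcoxon signed-rank, n = 19 pairs, two-sided 0.05, normal differences, 4000 runs (Monte Carlo standard error at most √(0.25/4000) = 0.008). Shifts are in SDs of the paired difference.

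| Scenario | Proportion with p < 0.05 |
|---|---|
| No true effect, handling error equal at both visits | 0.0495 |
| True shift 0.7 SD, no added error | 0.80 |
| True shift 0.7 SD, error doubles the variance of the difference | 0.52 |
| No true effect, systematic visit difference 0.25 SD | 0.18 |
| No true effect, systematic visit difference 0.50 SD | 0.53 |
| No true effect, systematic visit difference 0.75 SD | 0.86 |

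**5. Could a systematic difference arise?** The article does not show one, but leaves routes open. If both visits are assayed in one batch, baseline serum will have been stored about 16 weeks longer than post-treatment serum. Control samples come from routine follow-up visits, where the draw may be handled differently. Blinding the analysts does not remove differences that arise at the draw or in storage.

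**The case against.** **The aim is general oxidative status.** The panel's stated aim is oxidative and inflammatory status, and the description of GSH may only explain what the molecule does. Nrf2 appears in a separate hypothesised pathway, as a local mucosal event that red cells would not sample either. This stands: the article does not say that these three markers are meant to prove Nrf2 activation, and a reader who infers that goes beyond the text.

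**Handling steps belong in laboratory procedures.** Clotting time, thiol stabilisation, haemolysis checks and rejection rules are details an article may leave out. This also stands, and their absence is not the point made here. The specimen is stated, however, and no way of handling serum restores a pool removed with the cells.

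**Serum may be a loose label.** The same panel includes the erythrocyte sedimentation rate, which needs whole blood, so an anticoagulated tube may already be drawn. That is possible, but nothing in the article assigns such a tube to these markers, and the text would still need correcting.

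**The artefact is not shown to dominate.** A reader might infer that the pre/post result will reflect oxidation and leakage instead of any biological response. The documents do not support that: the range above starts near zero, and equal error at both visits leaves the false-positive rate near 5%. Nor can a specific power be attached to serum as opposed to cells, because the attenuation would have to be postulated.

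**The reach is small.** Three of eight oxidative markers, in a secondary endpoint of a pilot that disclaims definitive causal conclusions. This is correct.

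**Conclusion.** The concern holds as a mismatch between specimen and interpretation. Three largely intracellular markers are specified in stored serum, so a pre/post or between-group difference in them cannot be taken as a cellular antioxidant response and is open to pre-analytical artefact. This part rests on the article's own wording, on what serum is, and on the general laboratory premise that SOD and catalase in blood are mainly intracellular.

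The size of the artefact cannot be fixed from the documents. It depends on concentrations, lysis rates and handling that they do not give. If the error is equal at both visits the price is lost power. Spurious significance needs a systematic difference between visits or groups, which is possible but not shown. The primary microbiota and toxicity endpoints are untouched, as are the other five oxidative markers. It is a modest but worthwhile correction to a secondary endpoint.

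**What to change.** Decide before the first baseline draw, because stored serum cannot be converted later. Amend the biomarker endpoint text, the assay list and the panel description in section 5, and Table 1, in one of two ways.

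1. **Name a cell fraction.** For GSH, SOD and catalase, specify stabilised whole blood or red-cell lysate, normalised to haemoglobin, from one extra tube at the existing draw: baseline, week 16 and the control visit. This gives a blood-cell reading; it is still not a mucosal one.
2. **Keep serum only.** Drop GSH, label SOD and catalase as extracellular activity, record a haemolysis index on each aliquot with an exclusion rule set before unblinding, and state that these markers will not be interpreted as evidence of a cellular or Nrf2 response.

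The first option costs one tube and a little same-day handling. The second costs one biomarker, a haemolysis reading and some wording. Neither changes the sample size, the visit schedule or the primary analysis.

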## Abstract

Background: Chronic pelvic toxicity induced by radiotherapy and/or chemotherapy (R/CIPT) is a debilitating sequela in gynecological cancer survivors, often refractory to conventional treatments and potentially linked to gut microbiota dysbiosis. Ozone therapy (OT), particularly rectal insufflation, demonstrates anti-inflammatory and redox-modulating effects through hormetic mechanisms (Nrf2 activation/NF-κB inhibition). We hypothesize that its clinical benefit is mediated, in part, by restoring gut microbial homeostasis. Objective: This manuscript proposes a clinical study to evaluate the impact of rectal OT on the gut microbiota of patients with gynecological cancers and chronic R/CIPT. Proposed Methods: A prospective, observational study of 38 patients is outlined: 19 with CTCAE v5.0 Grade ≥2 chronic R/CIPT receiving compassionate rectal OT (~40 sessions over 4 months), and 19 matched controls without toxicity. Stool samples for 16S rRNA sequencing will be collected from the OT group pre- and post-intervention and once from controls. Primary endpoints are changes in microbiota composition/diversity and pelvic toxicity scores (CTCAE v5.0, EORTC QLQ-CX24). Secondary endpoints include quality of life (EORTC QLQ-C30, EQ-5D-5L), anxiety/depression (HADS), and serum inflammatory/oxidative stress biomarker analysis. Anticipated Results and Conclusion: This will be the first study to prospectively investigate whether rectal OT’s effect correlates with a beneficial shift in the gut microbiota, specifically an increase in commensals (e.g., short-chain fatty acids producers) and a decrease in pathobionts. If successful, OT could be assessed as a novel, microbiota-targeting intervention for R/CIPT. The findings from this pilot study will provide the necessary groundwork for a future randomized controlled trial to definitively establish causality and efficacy.

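### One two-sided 0.05 threshold covers every test, while the primary endpoint is an open set of taxa, diversity indices and two toxicity instruments with no hierarchy or multiplicity control

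*Protocol article*

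**What the plan says.** All references are to the protocol article.

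- **Threshold.** Section 5, Statistical Approaches, treats p-values "less than 0.05 will be considered significant, and all hypothesis tests will be conducted two-sided". Table 1 repeats p < 0.05 beside "Non-parametric tests (Wilcoxon, Mann–Whitney U) due to small sample size". Neither place mentions an adjustment, an order of testing or an exploratory status.
- **Primary endpoints.** The Abstract states: "Primary endpoints are changes in microbiota composition/diversity and pelvic toxicity scores (CTCAE v5.0, EORTC QLQ-CX24").
- **Microbiological primary.** Section 5 analyses composition and diversity through "Differential abundance of key taxa (e.g., Faecalibacterium, Roseburia, Akkermansia vs. Proteobacteria), and alpha/beta-diversity indices". The taxa are examples, and the number and choice of indices are not given.
- **Clinical primary.** Section 5 gives "Pelvic and gynecological toxicity grade measured by: (1) CTCAE v5.0 scale, and (2) EORTC QLQ-CX24 module (cervical cancer-specific"), without selecting a score. The same section enrols cervical, endometrial, vulvar and vaginal cancers.
- **Tests.** The primary analysis is "Wilcoxon signed-rank for pre/post ozone, Mann–Whitney U for inter-group comparisons", followed by "Spearman correlations for microbiota-clinical parameter associations".
- **Use of significance.** In the limitations paragraph of section 5, the third limitation defers multi-omic work until it is known whether community structure changes significantly.

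**The concern.** A 0.05 threshold limits false positives to 5% for one test. Here it applies separately to each member of a primary family whose size is not fixed. The more taxa and indices that are examined, the greater the chance that some primary result crosses 0.05 by luck. Because the list is open, that chance cannot be calculated in advance, and a reader of the results could not tell a pre-chosen taxon from one picked afterwards.

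At stake is how far a significant microbiota result from 19 treated patients can be trusted. The plan uses that kind of result to decide whether multi-omic studies are warranted.

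**Working it through.** **The plan's own figure.** The only error rate stated is 0.05 per test, and it holds test by test. With n = 19 the exact two-sided Wilcoxon signed-rank test has size 0.0494. With 19 against 19 the exact Mann–Whitney test has size 0.0497. The individual tests are sound; the difficulty is how many there are.

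**Counting the named items (section 5).**
- Taxa named as examples: 4.
- Diversity: at least 1 alpha and 1 beta index, so 2.
- Toxicity instruments: 2, each counted once although QLQ-CX24 has no single score selected.
- Pre/post family in the ozone group: 4 + 2 + 2 = 8 tests.
- One inter-group comparison for the 6 microbiota measures: 8 + 6 = 14 tests. Inter-group toxicity tests are left out because the groups are selected to differ on toxicity.
- The 14 named serum markers are not counted, because they are secondary.

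**Independent measures.** The chance of at least one p < 0.05 among k true null hypotheses is 1 − 0.95^k.
- k = 8: 1 − 0.95^8 = 1 − 0.663 = 0.337. Expected false positives: 8 × 0.05 = 0.4.
- k = 14: 1 − 0.95^14 = 1 − 0.488 = 0.512. Expected false positives: 14 × 0.05 = 0.7.
- With the exact test sizes above, the figures are 33.3% and 50.9%.

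**Correlated measures.** The planned rank tests were simulated with 19 treated patients and 19 controls. The assumptions, none of which the document supplies, are equal correlation between measures, pre/post correlation of 0.5 and no ties. Repeat runs differ by about one percentage point.

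| Correlation between measures | 8 tests, pre/post | 14 tests, with one inter-group contrast |
|---|---|---|
| 0 | 33–34% | 49–50% |
| 0.3 | 30–31% | 46% |
| 0.5 | 26% | 40% |
| 0.8 | 16–17% | 27–28% |

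The 8-test column assumes no ozone effect. The 14-test column also assumes no microbiota difference between the toxicity group and controls.

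**A longer taxa list.** If the examples grew to 20 taxa (an assumption), the pre/post family would be 20 + 2 + 2 = 24 tests. The chance would be 70%, 60%, 49% and 27% at correlations 0, 0.3, 0.5 and 0.8.

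**The case against.** **A later analysis plan may supply the adjustment.** The article is condensed, and a 0.05 threshold is compatible with adjusted p-values. This has force: a full plan that adjusts would settle much of the matter. But the article is not simply silent. It sets one threshold for all tests, repeats it in Table 1, and leaves the primary endpoint itself open.

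**The count can be inflated.** This stands. A reader might count three contrasts (pre/post, pre against control, post against control) for six microbiota measures plus two instruments, reach 6 × 3 + 2 = 20 tests, and conclude from 1 − 0.95^20 = 64% that a false positive is more likely than not. The documents do not support that reading:
- The contrasts share samples. Allowing for this gives about 57% with uncorrelated measures and 47% at correlation 0.5.
- A separate post-against-control comparison is never named.
- Pre against control addresses dysbiosis, not ozone. Section 2 argues that dysbiosis tracks symptom severity, so a real difference may be expected there.

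**No success rule is stated.** This also stands. A reader might infer from the conditional language about success in the Abstract and section 5 that any single significant result counts. The plan does not say so, and its hypothesis is directional. Counting only favourable results at 0.025 each, 8 independent tests give 1 − 0.975^8 = 18%.

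**It is a pilot.** The article says so, and it states that the design and sample size rule out definitive causal conclusions. Nor is the future randomised trial conditional on p < 0.05; it appears as a future direction. That lowers the consequence. It does not change the error rate, and the limitations do not mention multiplicity.

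**Conclusion.** The concern holds at moderate size. Following the plan as written, the chance of at least one nominally significant primary result with no ozone effect is about 34% for the 8 named pre/post tests if independent, and roughly 31% to 16% at correlations of 0.3 to 0.8. Even the lowest figure is over three times the nominal 5%. With one inter-group contrast added (14 tests) it is about 51% if independent, and 46% to 27% at those correlations. More taxa or indices would raise it.

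These figures rest on the minimum count, the assumed correlations and continuous measures. Ties in an ordinal grade such as CTCAE could shift them slightly.

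It would go too far to say that a false primary finding is more likely than not, or that the decision on a randomised trial turns on it. The documents tie only the deferred multi-omic work to significant change. The point should be fixed; it does not invalidate the study.

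**What to change.** Before any data are seen, amend Statistical Approaches and the endpoint paragraphs of section 5, the Abstract and Table 1:

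1. Name one primary microbiota measure, for example one stated alpha-diversity index, compared pre against post in the ozone group.
2. Name one primary clinical measure. CTCAE grade applies to all four tumour sites. Make QLQ-CX24 secondary, since the article itself describes it as "EORTC QLQ-CX24 module (cervical cancer-specific").
3. Test these two with Holm at 0.05 overall: the smaller p-value against 0.025 and, if that passes, the larger against 0.05.
4. Apply Benjamini–Hochberg false-discovery control within each of three families: taxa, serum biomarkers and correlations. Fix the taxa list or the rule that generates it.
5. Label all other p-values exploratory and report estimates with 95% confidence intervals, for example Hodges–Lehmann shifts.

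The cost is wording only: no extra patients, samples or assays. The downside is that fewer results can be called significant. The stricter thresholds remain reachable with 19 pairs: even Bonferroni over all 8 tests (0.05/8 = 0.00625) is attainable, with exact Wilcoxon size 0.0062.
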